## Methods and design

### The proposed trial

This will be an open-label randomized trial comparing five formulations of nitrates for their effects on bone turnover markers and headache. Because we will compare our results to our previous CIHR funded trial of NTG ointment, we have designed the trial to be as similar as possible to that earlier trial in study location, enrolment of the subjects, and choice of endpoints. We will recruit postmenopausal women age 50 years or older with no contraindications to using nitroglycerin (NTG). Our trial will consist of two phases. A run-in phase and a treatment phase, outlined below.

There are at least 13 nitrate formulations, each with varying doses. The comparative effects of available nitrate formulations have not been studied. Their effects on bone formation and resorption have not been compared. Their effects on headaches, the most common adverse effect, have not been evaluated and there are no data comparing the pharmacokinetics and little laboratory work relevant to selection of preparation or dose. Cellular, animal and human data suggest that effect of nitrates on bone is independent of formulation, but the dose should be low and the formulation used intermittently. However, it is possible that there might be some formulations that are preferred over others and the number of headache may vary by formulation. As such, before proceeding with a fracture trial, it is critical to identify the nitrate formulation that gives the greatest effects on bone turnover, with the fewest headaches, and is easy to use.

In selecting the formulations and doses to be tested in the current study we consulted with a group of scientists, including a cardiologist, a scientist who conducts cellular research in the area of nitric oxide, an internist, and a pharmacist/chemist. Our selections of formulations and dose were guided by several considerations. First, although we found strong effects of NTG ointment on bone, it is not an ideal preparation: approximately 2.5 cm (1 inch) is squeezed onto paper that is then taped to the skin. Participants complained of messiness, the paper sometimes falling off during sleep, and the dose being varied with different amounts squeezed onto the paper. Second, we include the 20 mg tablet of ISMO because it is convenient: we have previously shown that it increases markers of formation and decreases makers of resorption, and while it was a different study with a different design, the dropout due to headaches among women randomized to ISMO (20%); far less than what we observed during the run in phase with NTG ointment (about 40%) [48,54]. Third, we will use formulations that last 8 h or less because the sensitivity to effects of nitrates decreases with increasing frequency of dosing and continuous use (tachyphylaxis) [44]. Our data from the SOF found that women using nitrates intermittently had had significantly higher BMD than those who took them continuously [41]. Fourth, we have included sublingual tablets that produce a rapid peak effect because of the possibility that agents that induce bone formation might have greater effects if they rapidly reach peak levels with rapid offset, as has been shown for teriparatide [15]. This formulation was the most common one used by women taking intermittent nitrates in the SOF study. Fifth, we included a patch because it may have similar absorption of NTG as ointment but avoids the messiness. To preserve the 8-h duration, and minimize tachyphylaxis, we chose the highest-dose patch but will ask subjects to remove it by 8 versus 12 h. Finally, we will give the nitrate at bedtime as our earlier work demonstrated that taking the nitrate at bedtime resulted in a lower frequency of headaches than when taken in the morning.

We will start with a run-in phase to exclude women who would be unable to start the main trial because of headache. We will enroll about 420 women in the run-in phase, each to receive all of the 5 potential treatments (see below) in random order for 2 days each with 2-day washout period between treatments for a total of 18 days. The washout exceeds 10 half-lives of all of our formulations (which vary from 32 minutes in the case of sublingual NTG to 8 h for transdermal ointment) and will eliminate any carry-over effects [56-59].

Subjects will be seen at the start of the run in phase. We will take blood and urine for markers of bone turnover. Subjects will be given written and verbal instructions concerning the order of their treatment assignments, duration of the wash-out period and how to complete the VAS. We will also call subjects once at the start of the run in phase to confirm that the instructions have been understood and are being followed.

Those who tolerate all five formulations will enter the treatment phase and be randomly assigned to one of six groups: 0.3 mg sublingual nitroglycerin tablet, 0.6 mg of the sublingual tablet, a 20 mg tablet of isosorbide mononitrate, a 160 mg nitroglycerin transdermal patch (to be used for 8 instead of 12 h), and 15 mg of the NTG ointment used in the previous trial. To assure that the NTG ointment has the effects observed in our previous trial, we will also include a sixth randomized group to receive matching placebo ointment applied at night for about 8 h. All women will be randomized to receive one of the five formulations (or placebo) according to the randomization list provided by the study pharmacist (Sunnybrook Hospital, Toronto, Ontario, Canada). Women receiving the ointment formulation are blinded on whether they received the active NTG ointment or placebo. They will be unblinded, if they wish, upon study completion. We will continue enrolment until we have randomized 210 women, about 35 women per group. Concentrations of bone formation (BALP and P1NP) and bone resorption (CTX and NTX) will be measured in samples taken at study entry (at the start of the run in phase) and at 12 weeks. Subjects will record the number and severity of headaches on a daily basis during the run-in phase and then weekly after that. According to the product monograph, other possible events that are reported less frequently include: postural hypotension (lightheadedness going from lying/sitting to standing); increased heart rate; faintness; flushing; dizziness; nausea; vomiting and dermatitis (skin redness or irritation). To date, in our clinical trials we have not noted these less frequent adverse events. However, we will monitor for these effects.

Subjects will be seen again at the start of the treatment phase. At this visit, and as we did in our previous trial, we will administer the Block food-frequency questionnaire [60] to estimate dietary calcium and vitamin D intake and if required provide supplemental calcium carbonate (in 500 mg tablets) and vitamin D in 400 IU tablets as needed so that the total daily calcium intake for all study subjects will be 1,200 mg and the vitamin D intake will be 800 IU; these are the intakes recommended in the recently published guidelines for the prevention and treatment of OP in Canada [61,62]. Calcium and vitamin D are the mainstay of all treatment regimens for OP and any new agent should be evaluated to assess the additional benefit it would provide. Further, by providing calcium and vitamin D, we hope to discourage subjects who, after being enrolled in an ‘OP trial’, start taking additional, unreported calcium and vitamin D (cointervention). Calcium and vitamin D will be prepared and packaged by the study pharmacist (Sunnybrook Hospital, Toronto, Ontario, Canada), and instructions on how to take the supplements and the PI’s office number will be printed on each bottle. Subjects will be given standard verbal instructions by the research assistant and reminded to take the calcium and vitamin D daily with the morning meal. We will also provide the subjects with their treatment assignment and provide standard written (on the package and a information sheet) and verbal instructions on how to take the treatment. The treatment assignment will be prepared and packaged by our study pharmacist and the PI’s office number will be printed on each package.

Subjects will be called twice during the treatment phase: at 4 and 8 weeks after their visit. During these calls we will ask about the use of any new prescription and non-prescription medications; we will specifically ask about the use of any drugs for the treatment of OP, and about the use of calcium and vitamin D supplements. We will assess for possible adverse effects using a standardized, interviewer-administered questionnaire [63] (Additional file 1). We will first ask about any general adverse events. We then will ask specifically about headache, nausea, and dizziness (the three most common side effects associated with nitrate use [42]), and subjects who drop out due to nitrate-related adverse events will be followed daily until the adverse events have resolved. We will also ask about emergency room visits, hospitalizations, and visits to walk-in clinics (defined as severe adverse events), and the reason for these visits. The questionnaire we plan to use for assessment of adverse events was developed and validated in healthy postmenopausal women as part of [name]’s doctoral thesis [64]. Serious adverse events will be reviewed by the DSMB and decisions about continuing with the treatment assignment will be made on a case-by-case basis by the DSMB. We will see subjects at the end of the treatment phase and at this visit we will collect and count unused medication, calcium and vitamin D and administer our adverse event questionnaire. Our study design is illustrated in Additional file 1.

Our study pharmacist will use a computer-generated random number sequence to match each study identification number to treatment assignment for both the run in phase and the treatment phase.

Ideally, to protect against sources of bias, all of the treatments should be blinded. However, placebos for all formulations are unavailable, and it is not feasible to prepare new ones for this study. The primary outcome of change in markers of bone turnover is unlikely to be influenced by unblinded use of the formulations; note that technician who measures our markers will be blinded to treatment assignment. We recognize that reports of headaches are subjective and might be influenced by knowing the treatment assignment: a woman taking an ‘active’ drug might be more likely to notice headaches. We will note this potential bias as we consider the selection of the best preparation.

The run-in phase and treatment phase will have identical inclusion and exclusion criteria (Additional file 1). As in our previous trial, we will include women aged 50 years and older whose last menstrual period occurred at least 3 years ago. Those without a uterus will be eligible after age 55 years.

We will use the same exclusion criteria as in our previous trial: (1) women with a history of previous fracture; (2) those who report a diagnosis of osteoporosis (‘osteopenia’ will not be excluded) (note that we did consider measuring BMD at entry to the study to exclude women with low BMD as it is not feasible within the budget; if a woman has low BMD not identified at study entry, her risk of fracture during a 12 week trial would be very low); (3) a history of disorders such as hyperparathyroidism or Paget’s disease; (4) treatment within 12 months of study entry with any agent that may influence bone metabolism including any hormone, antiestrogen or raloxifene, prednisone (equivalent to 5 mg/day for 12 months or greater), lithium, or serotonin reuptake inhibitors; (5) treatment with any oral bisphosphonate, including alendronate, risedronate or etidronate use for at least 4 weeks, within the last 3 years and any previous treatment with the very long-lasting intravenous zoledronate; (6) treatment with parathyroid hormone or denosumab within the past 12 months; (7) current treatment with nitrates; (8) any history of migraine headaches (nitrates can exacerbate migraines); (9) history of angina or cardiovascular disease; (10) inability to give informed consent; and (11) hypersensitivity to nitroglycerin.

### Outcomes to be assessed

#### Run-in phase

During the run-in phase, subjects will receive, in random order, each of the five nitrate formulations for 2 days with a 2-day wash out period between formulations. We anticipate potential dropouts of participants both during the run-in and prior to the intervention phase, with main reason for discontinuing the study being headaches. We will immediately discontinue participants who have severe headaches with any of the formulations as a contraindication for any use of nitrates. To maximize efficiency and minimize dropouts, participants will be able to continue into the treatment phase immediately upon completion of the run-in phase.

Subjects will record the severity of headaches upon awakening every day during the run-in phase using a VAS (Additional file 1). The VAS has documented reliability, can detect subtle changes in headache and has been used in several studies, including our earlier CIHR funded study, designed to study the effects of NTG ointment on headache in healthy women [54,58,59]. To help establish the preferred preparation, every participant will be asked to rate and rank the five formulations and write comments about their acceptability for long-term use. We will also use these data together with the mean headache score (for each subject over the treatment periods and then the mean headache score considering all subjects in each of the treatment groups), to determine which formulations, if any, will not be continued in the treatment phase. As we aim to assess treatment options with reasonably broad acceptability, if there is one formulation that gives headaches in more than 75% of subjects in the run-in phase in the first 6 months of recruiting or is uniformly disliked in terms of mode of application, then we will eliminate that arm from our intervention phase. However, previous studies suggest that rate of headache will not be this high and individual preferences are likely to vary enough to merit consideration of effect, and we anticipate carrying forward all formulations to the intervention phase.

### Treatment phase

We will determine the percentage change, from baseline, in two markers of bone resorption (CTX and NTX) and two markers of bone formation (BALP and P1NP) among each of the five treatment arms and the placebo arm; we measured BALP and NTX in our previous study and the International Osteoporosis Foundation has now proposed that all trials include P1NP and CTX [65]. All four markers will be measured on samples drawn at the start of the run-in phase, as it is possible that there will be an effect on bone turnover with the short bursts of nitrate treatment during the run-in phase, and again at the final 12-week visit. We will measure CTX by electrochemiluminescence immunoassay (Roche Elecsys, Roche Diagnostics, Germany); the interassay coefficient of variation (CV) is 4.7%. We will measure NTX by enhanced chemiluminescence immunoassay (Vitros ECi, OrthoDiagnostics, USA); the interassay CV is 7.9%. P1NP will be measured by electrochemiluminescence immunoassay (Roche Elecsys, Roche Diagnostics); the interassay CV is 9.1%. BALP will be measured by paramagnetic particle immunoassay (Access 2, Beckman Coulter); interassay CV: 7.5% [66]. To minimize variability, we will collect fasting serum samples and second morning urine samples, store them at -70°C, and analyze all the samples together in a single laboratory at study completion.

Note that bone turnover markers allow us to assess the effects of treatment by 12 weeks. We recognize that bone markers are biomarkers for the clinical outcome of interest (fracture). However, a phase II trial of dose selection using change in BMD or bone geometry as endpoints would be prohibitively large, long, and expensive. Further, recent data suggest that higher levels of some bone resorption markers predict fractures independently of BMD [67,68] and with antiresorptive therapy greater treatment-related decreases in bone turnover are associated with a decreased risk of vertebral and non-vertebral fracture [69,70].

Note that all our trial protocol has and will continue to be conducted in accordance with the Helsinki declaration [71]. Our protocol has been reviewed and approved by the appropriate institutional research ethics boards (Women’s College Hospital and The University of Toronto) and all subjects are required to provide written informed consent before participating in our study.

### Sample size and analyses

We will use the ‘multiple comparisons with the best’ (MCB) approach for data analyses and determination of sample size [72]. We will give primacy to differences in bone formation (measured as percentage change over baseline) because this is the unique effect of nitroglycerin and the one most likely to reduce the risk of non-vertebral fracture. We wish to be able to estimate differences between formulations in percentage change over baseline to within plus or minus 15% assuming a standard deviation of percentage change of 25%. These assumptions are based on prior studies of bone turnover markers that have reported a minimal of 15% change in response to treatment and similar changes in SD [64,73-77].

At the analysis stage, MCB guarantees that differences between preparations will be estimated to within plus or 15% with 95% confidence (over all the comparisons made). These intervals result in one of the following conclusions: (a) a preparation is not the best (that is, does not increase formation the most), (b) a preparation is better than all the rest, or (c) the preparation might be best and is within 15% of the best.

At the design stage, MCB guarantees that if the best preparation is at least 15% better than the next best preparation, it will be ranked as best with probability at least 0.95. Based on these considerations, we require 30 subjects per group or 180 subjects total complete the study. We assume a dropout of rate of 10% post randomization, so we will enroll 210 subjects, approximately 35 per group. If one preparation is determined best by MCB, we will select that preparation. However, a possible result is that multiple preparations will be within 15% of the best. In that case we will rank preferred formulations based on their acceptability and tolerability; that is, the ISMO tablet may be preferred for its convenience and familiarity if it is nearly as good as the best. Thus, MCB allows consideration of other factors in deciding the preparation to be selected. Our MCB strategy allows practical consideration of ease-of-use and tolerability to guide selection of the preparation for future studies. If two or three preparations have similar effects on bone formation (do not differ by at least 15%), we will use tolerability data and subject preference from the run-in and previous studies to guide our choice. We expect the decision may benefit from the input of experts in osteoporosis and note that additional studies might be useful to select an ideal preparation and dose.

Our sample size was determined using STATA V. 10 on the basis of assessing the treatment effect. However, there is some likelihood we will need to consider other variables if there are multiple treatments that are within 15% of the best. The limiting factor in comparisons will be headache prevalence, but with given sample size (420 in the run-in) we will have power of at least 0.8 to detect a difference in prevalence of 10% with α = 0.05.

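### MCB on unadjusted percentage change uses the measured baseline inefficiently; baseline-adjusted means would sharpen the comparison of formulations at almost no cost

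*Protocol article*

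**What the plan says.** The protocol article, under Sample size and analyses, fixes both the method and the scale. On method: "We will use the ‘multiple comparisons with the best’ (MCB) approach for data analyses and determination of sample size". On the deciding outcome: "We will give primacy to differences in bone formation (measured as percentage change over baseline"). The tolerance and the spread are set on the same scale: "We wish to be able to estimate differences between formulations in percentage change over baseline to within plus or minus 15" per cent, "assuming a standard deviation of percentage change of 25" per cent. Two guarantees follow. Intervals are to hold "with 95% confidence (over all the comparisons made"), and a preparation at least 15% better than the next is promised that "it will be ranked as best with probability at least 0.95".

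The Treatment phase section applies percentage change to all four markers ("We will determine the percentage change, from baseline, in two markers of bone resorption (CTX and NTX", then BALP and P1NP), "among each of the five treatment arms and the placebo arm". All four are measured at the start of the run-in and at 12 weeks. Thirty completers per group are required. The article names no covariate, model or transformation, and rules none out.

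**The concern.** Percentage change divides by baseline, which implicitly assumes that the 12-week value moves in full proportion to it. When the correlation between the two log values is below 1, this over-corrects: women who happen to start low tend to show larger percentage rises. The correlation must be below 1 here, because the plan assumes a 25% SD of change and reports interassay CVs of 7.5% (BALP) and 9.1% (P1NP).

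An arm of about 30 that starts low by chance therefore tends to rank higher on bone formation. The formulation for a fracture trial is chosen from this comparison, and the baseline needed to remove that noise is already collected.

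**Working it through.** **1. The plan's own figure.** Inputs from Sample size and analyses: SD 25, margin 15 (read as percentage points), 95% joint confidence. There are six groups, counting placebo. The MCB formula is n = 2(d × SD / margin)², where d is the one-sided constant for five comparisons with correlation 0.5. With d = 2.234, n = 2(2.234 × 25/15)² = 27.7, or 29 with the t-based constant. The plan's 30 is reproduced. At n = 30 the half-width is 2.25 × 25 × √(2/30) = 14.5 points, and the probability of correct selection is 0.960. Both targets are met.

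**2. Gain from adjustment.** Let ρ be the baseline-to-12-week correlation on the log scale, with equal log variance at both times. The variance of log change is proportional to 2(1 − ρ), and that of ANCOVA to 1 − ρ². Their ratio is (1 + ρ)/2, so the reduction is (1 − ρ)/2.

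**3. Linking ρ to the stated SD.** The article gives neither ρ nor a between-woman CV, so the CV is an assumption. Taking the SD of change as 25%, ρ = 1 − ln(1 + 0.25²) / [2 ln(1 + CV²)]. The simulated column compares log ANCOVA with raw percentage change for log-normal markers in six arms of 30.

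| Assumed baseline CV | ρ | Formula reduction | Simulated reduction |
|---|---|---|---|
| 25% | 0.50 | 25% | 24% |
| 30% | 0.65 | 18% | 18% |
| 35% | 0.74 | 13% | 15% |
| 40% | 0.80 | 10% | 11% |
| 50% | 0.86 | 7% | 8% |

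A separate six-arm simulation put the top of the range at about 26%, hence 8% to 26%. If ρ is 0.90 or 0.95, the formula gives (1 − 0.90)/2 = 5% or (1 − 0.95)/2 = 2.5%.

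**4. The mechanism.** In the simulations at SD 25, the between-arm difference in percentage change correlated −0.23 to −0.49 with the chance baseline difference. In a companion two-arm simulation, the ANCOVA estimate correlated about 0 with it. Squaring gives 0.23² = 0.05 and 0.49² = 0.24, so adding log baseline to the percentage-change model should remove roughly 5% to 24% of the variance. That is most of the gain.

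**5. What it buys at SD 25.** With a 25% reduction (ρ = 0.50), the half-width falls to 14.5 × √0.75 = 12.6 points and the probability of correct selection rises from 0.960 to 0.984. With a 10% reduction (ρ = 0.80), they are 13.8 points and 0.971.

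**6. If the SD is larger.** The Research to date section reports BSAP differences from placebo in the earlier 12-week ISMO trial with 95% CIs of 8.9 to 37.8 and 1.1 to 30.7. Assume 48 women per arm (48 on placebo; 96 on ISMO split equally). The first CI implies an SD of (28.9/2)/1.96/√(2/48) = 36, and the second (29.6/2)/1.96/√(2/48) = 37. Allowing for that trial's dropouts, with an assumed split between arms, gives 32 to 34. At SDs of 32 to 36 and the same CVs, the simulated reduction is about 13% to 47%.

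**The case against.** The strongest reply is that nothing is wrong on the planned scale: 30 per group delivers ±15 points and 0.95 at SD 25, and adjustment lifts an already adequate selection probability by only a point or two. That stands, and it limits the point to efficiency.

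Percentage change does use the baseline, and the article does not exclude a covariate, which an unseen SAP could add. That also stands. However, the article fixes the scale and the margin, so moving to ratios of geometric means would depart from its text.

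A reader might infer that baseline imbalance biases the ranking, or is a harm on top of lost precision. Neither follows. Under randomization the imbalance is chance, it is already contained in the SD of percentage change, and removing it is the same benefit as the variance reduction.

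A reader might also infer a firm gain of a third or more. That needs either a larger SD than the plan states or a baseline CV below 25%, and the article supplies no CV.

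The log scale changes the margin. A ratio of 1.15 equals 15 points only against a comparator with no change. Against a rise of 23.3%, as reported for BSAP on ISMO 20 mg versus placebo, it is 1.233 × 15 = 18.5 points. Percentage change also serves comparison with the earlier ointment trial, to which endpoints were deliberately kept similar.

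Finally, preparations within 15% of the best are separated on acceptability and tolerability, so marker rank alone does not decide.

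**Conclusion.** The point holds as an efficiency improvement. MCB on unadjusted percentage change carries avoidable noise from chance baseline differences, and adjustment was more precise in every setting tried.

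At the stated SD of 25%, the variance of between-arm differences falls by about 8% to 26% for assumed baseline CVs of 25% to 50%, and by about 5% or less if the correlation is 0.90 to 0.95. It falls by more if the SD is larger. These figures rest on log-normal markers, equal log variance at both times and the assumed CVs, none of which the article states.

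The documents do not support reading this as a sample-size error or as precision below what is claimed at SD 25%. Whether 25% is itself too small is a separate question; here it affects only the size of the gain.

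**What to change.** State that MCB is run on baseline-adjusted means, in one of two forms:

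- **Preferred:** ANCOVA of the log 12-week marker on arm and log baseline, with MCB on the adjusted means, back-transformed to percentage differences in geometric means. Restate the 15% tolerance as a ratio and justify it on that scale.
- **Keeping the present scale:** add log baseline as a covariate to the percentage-change model and leave the 15-point margin as it is.

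In either case, keep raw percentage change by arm as a descriptive table for comparison with the earlier ointment trial. If an unseen SAP already adjusts for baseline, align the protocol wording with it.

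The cost is analysis wording plus, for the log version, a new justification of the margin. No extra women, samples or visits are needed.

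### MCB conclusion (c) claims closeness to the best that, at 30 per group, the intervals support only for the observed leader or a virtual tie

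*Protocol article*

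**What the plan says.** All of this stands in the protocol article, Sample size and analyses. The method is fixed there: "We will use the ‘multiple comparisons with the best’ (MCB) approach for data analyses and determination of sample size". The aim is to "estimate differences between formulations in percentage change over baseline to within plus or minus 15" percent, "assuming a standard deviation of percentage change of 25" percent. Bone formation is the outcome given primacy.

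For the analysis the section promises that "differences between preparations will be estimated to within plus or 15% with 95% confidence (over all the comparisons made"). It then says the intervals lead to one of three conclusions: (a) a preparation is not the best, (b) it is better than all the others, or "c) the preparation might be best and is within 15% of the best".

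The selection rule builds on this. If MCB identifies one preparation as best, it is chosen. Otherwise "a possible result is that multiple preparations will be within 15% of the best", and acceptability and tolerability decide. The plan's own example is a tablet preferred for convenience if it is nearly as good as the best. The same condition is later restated as preparations not differing by at least 15%, without saying whether the estimate or the confidence limit is meant.

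**The concern.** Not being excluded as best and being close to the best are answered by opposite ends of the MCB interval. The upper limit shows whether a preparation can still be the best. The lower limit shows how far behind the best it could be. Conclusion (c) draws the second statement from the first.

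The tie-break exists so that a preparation other than the observed leader can be chosen, and for such a preparation the 15% assurance generally fails. The formulation taken into the fracture trial could be reported as within 15% of the best, apparently with 95% confidence, when its interval allows a much larger deficit. For scale, the Research to date section reports a 23.3% increase over placebo in the bone formation marker for 20 mg ISMO.

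**Working it through.** **Inputs** (Sample size and analyses unless noted): SD of percentage change 25; margin 15; simultaneous confidence 95%; 30 completers per group and 180 in total, hence six groups. Treatment phase also names five treatment arms and a placebo arm. The text does not say whether MCB covers the placebo arm, so both k = 5 and k = 6 are shown. All differences are percentage points of change from baseline.

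**Interval.** Let D be a preparation's observed mean minus the best observed mean among the others. The MCB interval for the corresponding true difference runs from min(0, D − h) to max(0, D + h). Here h = d × SD × √(2/n), and d is the one-sided 95% Dunnett quantile for k − 1 comparisons with k(n − 1) degrees of freedom.

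**The plan's own figure.** At n = 30, 25 × √(2/30) = 6.455.
- k = 5: d = 2.179, h = 2.179 × 6.455 = 14.07.
- k = 6: d = 2.251, h = 2.251 × 6.455 = 14.53.

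With six groups, h first falls below 15 at n = 29 (14.78). The design-stage requirement, 2 × (2.234 × 25/15)² = 27.7, gives 28. So 30 per group reproduces, and one-sided MCB is evidently the method behind it.

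**What conclusion (c) needs.** Call a preparation retained if its upper limit is above 0, that is, D > −h.
- The observed leader has D > 0, so its lower limit is no worse than −h, which is above −15.
- Any other retained preparation has D between −h and 0, so its lower limit D − h lies between −h and −2h. That is −14.1 to −28.1 (k = 5) or −14.5 to −29.1 (k = 6).
- A lower limit above −15 needs D > h − 15, that is, D > −0.93 (k = 5) or D > −0.47 (k = 6). Only a virtual tie with the leader meets this.

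**How often it matters** (200,000 simulated trials, n = 30, SD 25).
- Five equal preparations: on average about 4.75 are retained, about 1.3 have a lower limit above −15, and the median of the worst retained lower limit is −23.5.
- Probability that a preparation truly worse than the best by a given amount is retained, in the setting where the best stands alone at the top:

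| True deficit (points) | k = 5 | k = 6 |
|---|---|---|
| 18 | 0.27 | 0.30 |
| 20 | 0.18 | 0.20 |
| 22 | 0.11 | 0.12 |
| 25 | 0.05 | 0.05 |
| 28 | 0.016 | 0.019 |

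- If all rivals are truly 20 points worse, at least one is retained in 41% (k = 5) or 48% (k = 6) of trials.

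**What would make (c) true as written.** Every retained preparation has a lower limit above −15 only if 2h ≤ 15. That needs n = 2 × (2 × 2.160 × 25/15)² = 103.7, about 104 per group (k = 5), or with 2.234, 110.9, about 111 per group (k = 6).

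**The case against.** The best defence is that being within 15% of the best describes the observed difference. Retention means D > −h with h about 14 to 14.5, so nearly every retained preparation does have an observed difference below 15 (99.8% to 99.9% in simulation with equal means). The three conclusions then cover practically every case, and the restated tie-break condition fits. This reading is possible, but the conclusions follow directly on a 95% confidence guarantee and are said to result from the intervals, and an observed difference below 15 carries no such guarantee. A preparation truly 20 points worse shows an observed difference below 15 with probability 0.22, and its lower limit can still reach about −29. If instead both halves of (c) must hold as confidence statements, a preparation with D between −h and about −0.5 to −0.9 fits none of the three conclusions.

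The defence is right that selection is not mechanical: the plan asks that the chosen preparation be nearly as good as the best, calls for expert input and allows for further studies.

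A reader might also infer two further errors that the text does not contain:
- The statement that a best preparation with a 15% lead means "it will be ranked as best with probability at least 0.95" is correct. The probability at n = 30 is 0.966 (k = 5) or 0.960 (k = 6), and the plan does not claim 0.95 for being declared sole best by MCB.
- The confidence statement "with 95% confidence (over all the comparisons made") need not promise 15% precision for every pair of preparations. Under a method named for comparisons with the best, the comparisons made are those with the best.

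**Conclusion.** The point holds. Conclusion (c) attaches a 15% closeness claim to every preparation not excluded as best. With 30 per group, the intervals give that claim 95% confidence only for the observed leader or a preparation within about 0.5 to 0.9 points of it. For the other retained preparations the lower limit lies between about −14 and −28 points (five preparations) or −15 and −29 (six groups). Because the claim feeds the tolerability tie-break, it affects a stated decision rule.

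Two stronger conclusions are tempting and unsupported. The trial is not likely to select a preparation 28 points worse: that figure is a worst-case simultaneous limit, and a preparation truly that far behind is retained in under 2% of trials. The realistic concern is a true deficit of about 20 points, retained in up to 18% to 20% of trials. Nor is the sample size wrong, since 30 per group delivers the half-width it was set to deliver.

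The figures assume a pooled SD of 25, 30 completers in every group and normally distributed group means. The limits scale with the SD actually observed.

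**What to change.** In Sample size and analyses:
1. Reword (c): *the preparation cannot be excluded as best; its MCB lower limit is the largest loss versus the best compatible with the data*.
2. There and in the selection rule, use *within 15% of the best* as a confidence statement only when that lower limit is above −15%. If the tie-break is meant to use observed differences below 15%, say so and do not attach the 95% guarantee.
3. Report the MCB lower limit of whichever preparation the tolerability tie-break selects.

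The cost is wording and one reporting rule. No extra participants or new analysis are needed, because the limit is already part of the MCB output. The downside is that fewer preparations can be called within 15% of the best, often only the leader. Enlarging the trial to about 104 to 111 per group would make (c) true as written, but that is not needed to repair the claim.
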